### Randomisation

Randomisation is performed during surgery by accessing a central internet-based randomisation program. Randomisation is stratified for hospital, patient's age and history of tubal pathology (i.e., previous EP, previous tubal surgery, and previous pelvic inflammatory disease).

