### Outcome measures

#### Primary outcome measure

The primary outcome measure is the time to the occurrence of a spontaneous viable IUP. A viable IUP is defined as a pregnancy visible at ultrasound at a gestational age of ≥ 12 weeks with fetal cardiac activity, or the delivery of a child. If an IUP does not occur, follow-up ends on the day of the last consultation.

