### Statistical analysis

The analysis is performed according to the *intention to treat *principle. Short term outcome measures are expressed in RR and their 95% confidence intervals.

Future fertility is assessed by means of life table analysis. Kaplan-Meier curves are constructed, estimating the cumulative probability of spontaneous IUP and repeat EP over time. The assessment of fertility status is censored for those periods when women used contraceptives or did not have sexual intercourse. In case a spontaneous viable IUP does not occur, follow up ends at the last date of consultation, or at the moment when either IVF or tubal surgery is performed. Spontaneous conceptions that occur after failed IVF treatment will be registered, but these pregnancies will not be considered as endpoint in the analysis. The log-rank test is used to test differences between the Kaplan-Meier curves for statistical significance. The differences between both treatment modalities are expressed as a FRR with 95% confidence interval, calculated through Cox proportional hazard analysis.

A cost-effectiveness analysis will be performed within a decision analysis framework, based on outcome of costs per live birth, including IVF programs in case a spontaneous pregnancy does not occur.

Patient's preferences will be analysed by differences in outcome of the DCE.

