### Sample size

The IUP rate after salpingectomy is assumed to be 40% after 36 months and the median time to pregnancy in this group is 1.4 year [8]. We consider an increase of the IUP rate by 10–15% after salpingostomy compared to salpingectomy clinically relevant to overcome the disadvantages of persistent trophoblast and repeat EP. In order to prove a reduction of the median time to pregnancy from 1.4 year to 1 year, 225 patients in each group are required (significance level of 5%, a power of 80%, and 5% loss to follow up in both groups, 2-sided test).

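### Randomisation is stratified by hospital, age and tubal history, but the primary log-rank test and Cox model as named do not use these factors, which may give up a little power

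*Protocol article*

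**What the plan says.** Under Randomisation, the protocol article states: "Randomisation is stratified for hospital, patient's age and history of tubal pathology". It lists previous ectopic pregnancy, previous tubal surgery and previous pelvic inflammatory disease as the tubal history. The age cut, block size and number of hospitals are not given.

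Under Primary outcome measure: "The primary outcome measure is the time to the occurrence of a spontaneous viable IUP".

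Under Statistical analysis, the comparison is fixed in two sentences. The first is "The log-rank test is used to test differences between the Kaplan-Meier curves for statistical significance". The second says that the treatment difference is "expressed as a FRR with 95% confidence interval, calculated through Cox proportional hazard analysis". Neither names a stratum or a covariate. Age and previous ectopic pregnancy come back only under Subgroup analyses.

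Under Sample size, the design aims to show "a reduction of the median time to pregnancy from 1.4 year to 1 year" with 225 women per group ("significance level of 5%, a power of 80%, and 5% loss to follow up in both groups, 2-sided test"). The same paragraph also says: "The IUP rate after salpingectomy is assumed to be 40% after 36 months".

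**The concern.** Stratified randomisation forces the arms to be alike on the stratification factors. If those factors predict the outcome, the treatment contrast varies less from trial to trial than under simple randomisation. An unstratified log-rank test does not know this. It uses a variance that still contains the between-stratum differences, so its p-values tend to be slightly too large. A Cox model with treatment alone also estimates a marginal ratio, which lies closer to 1 than the ratio within strata.

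What is at stake is some power in the primary comparison, given up although the factors are known for every woman at randomisation. The protection against a false positive result is not affected.

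**Working it through.** **The plan's own figure.** A fall in the median from 1.4 to 1 year is a rate ratio of 1.4 under exponential times. Events needed (Schoenfeld): 4 × (1.960 + 0.842)² / (ln 1.4)² = 278.

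- On the medians, 36-month event probabilities are 1 − 2^(−3/1.4) = 0.774 and 1 − 2^(−3) = 0.875, mean 0.824. Then 278 / 0.824 / 0.95 / 2 gives 178 per group.
- On the 40% control rate, they are 0.40 and 1 − 0.6^1.4 = 0.511, mean 0.455. The same steps give 322 per group.

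The stated 225 lies between and is reached only with unstated accrual assumptions, for example 226 with 3 years' accrual and at least 0.5 year of follow-up. With 450 × 0.95 = 427.5 women, expected events are 352 (medians) or 195 (40% rate). Power, Φ(√(events/4) × ln 1.4 − 1.960), is 88% or 65%. Both bases are therefore carried below.

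**Main simulation.** From the article: 450 women, 36 months, 5% loss, rate ratio 1.4. Assumed: permuted blocks of 4 within hospital × age × history; 10 or 40 hospitals; moderate prognosis (ratios 0.7 for age and 0.6 for history, hospital SD 0.2) or strong prognosis (0.5, 0.4, SD 0.4). U = unstratified, S = stratified by age × history, F = stratified by all three factors. Gaps are taken from unrounded values.

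| Hospitals, prognosis | Control basis | Type I % U / S | Power % U / S | Gap S − U | Power % F |
|---|---|---|---|---|---|
| 10, none | 40% rate | 5.0 / 4.9 | 64.8 / 64.6 | −0.2 | 62.7 |
| 10, none | 1.4 y median | 5.4 / 5.5 | 89.8 / 89.5 | −0.3 | 85.9 |
| 10, moderate | 40% rate | 4.4 / 4.9 | 64.1 / 65.8 | 1.7 | 64.8 |
| 10, moderate | 1.4 y median | 4.5 / 5.0 | 86.2 / 88.0 | 1.8 | 85.4 |
| 10, strong | 40% rate | 3.3 / 4.3 | 60.5 / 65.1 | 4.5 | 66.8 |
| 10, strong | 1.4 y median | 2.5 / 3.9 | 75.0 / 82.6 | 7.6 | 83.5 |
| 40, moderate | 40% rate | 4.9 / 5.1 | 65.3 / 66.7 | 1.4 | 58.1 |
| 40, moderate | 1.4 y median | 4.8 / 4.5 | 86.0 / 89.0 | 3.0 | 73.1 |
| 40, strong | 40% rate | 4.6 / 5.2 | 58.7 / 64.6 | 5.9 | 56.5 |

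There were 1,500 to 4,000 runs per setting. The simulation error is about 0.3 to 0.6 point for type I error and 0.5 to 1.3 points for power. The 3.0-point gap comes from a 1,500-run setting. The 5.4% in the second row is within error of 5%: the standard error is √(0.05 × 0.95 / 4000) = 0.34 point.

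**Simpler simulations.** These used 428 women, four age × history strata and a within-stratum ratio of 1.4.

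- Both factor ratios 0.7, 40% rate: power 64% unstratified against 65% stratified.
- Both 0.5, 40% rate: type I error 4.1% against 4.9% and power 60% against 65% in one set of runs; 4.2% against 5.1% and 61% against 64% in another.
- Both 0.5, 1.4-year median: 3.8% against 5.1%, and 81% against 87%.
- Both 0.4, 40% rate: power 59% against 65%.

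**Check of the mechanism.** With both ratios 0.5, the null standard deviation of the test statistic was 0.948 unstratified and 0.988 stratified. The implied two-sided levels are 2 × [1 − Φ(1.96/0.948)] = 3.9% and 2 × [1 − Φ(1.96/0.988)] = 4.7%, close to the simulated 4.1% and 4.9%.

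**Why hospital differs.** With two age groups, 40 hospitals make 40 × 2 × 2 = 160 strata, or 450/160 = 2.8 women each. Many strata then contribute no comparison. Against U, full stratification took power from 65.3% to 58.1% and from 86.0% to 73.1% (moderate), and from 58.7% to 56.5% (strong). With 10 hospitals it lost power or gained it, depending on prognosis.

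**The case against.** The strongest objection is that the omission is read from silence. The article never calls the analysis unadjusted, nothing in it excludes the factors, and a condensed article often leaves strata and covariates to an analysis plan, which is not shown here. A reader might infer that the authors decided to ignore the strata; the text does not support that. What remains is that the article does name the primary test. A log-rank comparison of the two arms' Kaplan-Meier curves is, read plainly, the unstratified one, and a better-matched test is available from data already collected.

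The second objection is that prognostic strength is unsourced. This stands. The Background compares the two operations by tubal history but gives no figure for how far history or age predicts conception. Excluding women with contralateral tubal disease may also narrow the spread. The size can only be given as a range that starts at zero.

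The third is that the planned change in medians is a marginal contrast, whereas the simpler simulations fix 1.4 within strata, which lowers the unstratified power somewhat. This is fair for the absolute levels. It does not remove the gap between two tests applied to the same trial.

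The fourth is that stratification is not free of judgement. This also stands where hospitals are many and small.

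**Conclusion.** The point holds as a low-severity, nearly free improvement. The randomisation uses three factors and the primary analysis as named uses none. If age and tubal history are prognostic, the named analysis is mildly conservative. The power given up is nil without prognostic effect, about 1 to 2 points if moderate, and about 4 to 8 points if strong. Single runs fell slightly outside these bands (3.0 points in a moderate setting, 3 in a strong one). The direction is secure; the size rests on assumed prognostic strengths and numbers of hospitals.

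Three stronger readings are not supported:

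- A reader might infer that the primary test is invalid. It is not: its type I error stays at or below 5%.
- A reader might infer that the test always runs below 5%. It does so only if the factors are prognostic.
- A reader might infer that the loss falls on a trial already short of power. That depends on which Sample size input is used: about 65% on the 40% rate, about 88% on the medians. The conflict between those inputs is a separate matter.

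**What to change.** State that the primary log-rank test is stratified by age group and history of tubal pathology, using the categories applied at randomisation, and that the FRR comes from a Cox model stratified by or adjusted for the same two factors. Report the unadjusted test and FRR as supportive.

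Do not stratify the test by individual hospital. Pool hospitals, for example by country, or deal with hospital in a sensitivity analysis.

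Settle this before comparative data are examined, including the interim analysis after 150 women. If an analysis plan already says this, nothing more is needed than agreement between the two documents.

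The cost is one or two sentences and no new data. With no prognostic effect, the two-factor stratified test lost 0.2 to 0.3 point of power in the simulations, which is within their error. The one small downside is interpretive: the adjusted FRR is a conditional ratio and need not equal the marginal one, so the report should say which is shown.

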### Sample size

The IUP rate after salpingectomy is assumed to be 40% after 36 months and the median time to pregnancy in this group is 1.4 year [8]. We consider an increase of the IUP rate by 10–15% after salpingostomy compared to salpingectomy clinically relevant to overcome the disadvantages of persistent trophoblast and repeat EP. In order to prove a reduction of the median time to pregnancy from 1.4 year to 1 year, 225 patients in each group are required (significance level of 5%, a power of 80%, and 5% loss to follow up in both groups, 2-sided test).

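### The two salpingectomy-arm inputs to the sample size contradict each other, and with 36 months of follow-up neither yields 225 per group for 80% power

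*Protocol article*

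**What the plan says.** The Sample size section of the protocol article gives two assumptions for the salpingectomy arm in one sentence: "The IUP rate after salpingectomy is assumed to be 40% after 36 months and the median time to pregnancy in this group is 1.4 year". It then sets the target: "We consider an increase of the IUP rate by 10–15% after salpingostomy compared to salpingectomy clinically relevant". The calculation itself is tied to the medians: "In order to prove a reduction of the median time to pregnancy from 1.4 year to 1 year, 225 patients in each group are required". Its other settings are 80% power, a two-sided 5% level and "5% loss to follow up in both groups".

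The primary outcome is a time to event (Primary outcome measure). Each woman is to be followed by six-monthly questionnaires for 36 months (Long term follow-up). The comparison is by log-rank test, with an FRR from a Cox model: "The log-rank test is used to test differences between the Kaplan-Meier curves for statistical significance".

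**The concern.** A median read from a Kaplan-Meier curve is the time by which half the group has had the event. If half have conceived by 1.4 years, the curve cannot stand at 40% at 3 years. So the two assumptions cannot both describe the curve that the log-rank test will compare, and this needs no model.

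The power of a log-rank test depends on the hazard ratio and the number of events. The two inputs imply very different numbers of events in the same women, so the stated 80% has no single basis.

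This matters for how the result is read. The Discussion says that if salpingostomy is not better, the cases of persistent trophoblast and repeat EP avoided by salpingectomy might decide the matter. A non-significant result judged against a claimed 80% power could be over-read as showing no benefit.

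**Working it through.** **Inputs.** From Sample size: 225 per group; two-sided 5%; 80% power; 5% loss; 40% at 36 months; medians 1.4 and 1.0 years; relevant gain 10 to 15 points. From Long term follow-up: 36 months per woman. Not stated, and assumed here: proportional hazards throughout, and exponential times where the medians are used. Under these, the medians give a hazard ratio (HR, the FRR of the Cox analysis) of 1.4/1.0 = 1.4.

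**1. The two inputs side by side.**
- Median 1.4 years, exponential: rate at 3 years = 1 − 0.5^(3/1.4) = 77.4%, not 40%.
- 40% at 3 years, exponential: median = 3 × ln 0.5 / ln 0.6 = 4.07 years, not 1.4.

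**2. Events needed for HR 1.4** (Schoenfeld): d = 4(1.960 + 0.842)² / (ln 1.4)² ≈ 277.

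**3. Attempt to reproduce 225.** Number per group = d / (sum of the two arms' 36-month event probabilities), divided by 0.95 for loss.

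| Base | 36-month rates | Per group | With 5% loss |
|---|---|---|---|
| Medians 1.4 vs 1.0 y | 77.4% vs 87.5% | 277/1.649 ≈ 168 | ≈ 177 |
| 40% base, HR 1.4 | 40% vs 1 − 0.6^1.4 = 51.1% | 277/0.911 ≈ 304 | ≈ 320 |

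Rounding events up, or using Freedman's formula (283 events), moves these to 178–181 and 322–328. One-sided versions give 140–143 and 254–258. A two-proportion test gives 409 per group for 40% vs 50% and 183 for 40% vs 55% (430 and 196 with continuity correction). None of these is near 225.

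**4. Power of 225 per group after 5% loss.** Women retained: 450 × 0.95 = 427.5, or 213.75 per group. Power = Φ(½√events × ln HR − 1.96).

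| Scenario | HR | Events | Power |
|---|---|---|---|
| Medians 1.4 vs 1.0 y, 36 months | 1.40 | 213.75 × 1.649 ≈ 352 | 88% |
| 40% vs 51.1% | 1.40 | 213.75 × 0.911 ≈ 195 | 65% |
| 40% vs 50% | ln 0.50/ln 0.6 = 1.357 | 192 | 56% |
| 40% vs 52.5% | ln 0.475/ln 0.6 = 1.457 | 198 | 75% |
| 40% vs 55% | ln 0.45/ln 0.6 = 1.563 | 203 | 89% |

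A log-rank simulation of the second row (214 per group) also gave 65%. On the 40% base, 80% power is reached at HR about 1.49, that is 40% vs about 53%.

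**5. What would give 225.** With HR 1.4 and 5% loss, about 65% of women must have an event. The 40% base gives (40 + 51.1)/2 ≈ 46%. Unstated settings that do reach about 225 are:
- exponential medians with about 1.8 years of follow-up (59.0% and 71.3% with an event);
- exponential medians with 3 years of uniform accrual and a 0.5-year minimum follow-up (59.3% and 70.2%);
- a two-proportion comparison of 40% vs 53.5% (226).

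The first two sit poorly with 36 months per woman and conflict with the 40% rate. The third is neither the stated effect nor the stated test.

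**The case against.** **The 65% is a hybrid.** It takes the hazard ratio from the medians and the base rate from the 40%, after those inputs have been shown to conflict. The article states neither a hazard ratio nor a 51% rate. This stands: 65% is one branch, and if the medians are kept with 36 months of follow-up, 225 is more than enough. A reader might infer that the trial has 65% power instead of 80%. The article does not support that as an unconditional statement.

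**80% power does fall inside the relevant range.** On the 40% base it is reached at a gain of about 13 points. This also stands; the shortfall is confined to the lower part of the range.

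**The 1.4 years may be the median among women who conceive.** That would remove the contradiction, and the cited source that could settle it is not at hand. But such a median does not define the effect a log-rank test compares. Simulation with 214 per group, a 40% salpingectomy rate, conditional medians of 1.4 and 1.0 years and truncated-exponential times (assumed) gave power of about 6% if salpingostomy also reaches 40%, 68% at 50%, 76% at 51%, 82% at 52% and 94% at 55%. Most of the range is then adequately powered, but the answer again turns on an IUP rate that the calculation does not name.

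**Staggered follow-up may lie behind 225.** The Abstract says up to 36 months, and an article may leave accrual assumptions to the full protocol. So 225 is not proved to be a miscalculation, and it would be wrong to say that only a 1.8-year follow-up produces it. What remains is that the inputs which are printed do not lead to it.

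**Planned censoring.** The Statistical analysis section censors periods of contraception or no intercourse and ends follow-up at IVF or tubal surgery. It is tempting to attach a further loss of power to this. The article gives no figure, and the 40% may already reflect similar censoring, so no size can be claimed.

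**Conclusion.** The point holds as an inconsistency in the stated inputs and a power claim they do not support. The contradiction between 40% at 36 months and a 1.4-year median is model-free if both describe the planned Kaplan-Meier curve.

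Under proportional hazards, 36 months per woman and 5% loss, 225 per group is above the roughly 177 needed on the exponential medians and below the roughly 320 needed for HR 1.4 on the 40% base. The corresponding power is about 88% or about 65%. On the 40% base the chance of missing a 10-point gain, which the protocol itself calls relevant, is about 44%.

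The documents do not show which input is the right one, so they do not establish that the trial is underpowered overall. They do show that the sentence claiming 80% power cannot stay as written.

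**What to change.** In Sample size:
- Reconcile the 40% rate and the 1.4-year median into one consistent set. If the median refers only to women who conceive, say so and do not use it as the log-rank effect.
- State the planned effect as an FRR, with the 36-month IUP rate in each arm, the required number of events and the follow-up assumed.
- Restate the power of 225 per group on that basis. If the 40% rate is kept, this is about 65% for FRR 1.4 (40% vs 51%), or 80% for FRR about 1.49 (40% vs 53%).
- Add, without a figure, that the censoring planned in Statistical analysis may lower the event count further.

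The change is to wording and figures only. It needs no extra patients and leaves the design and test as they are. The cost is that the stated power may become less favourable.

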### Interim analysis

An interim analysis will be performed after the inclusion of 150 women. This analysis will be done by an independent Data and Safety Monitoring Committee (DSMC) that will not be aware of the allocation of treatment. The statistical analysis will be performed according to O'Brien Fleming's rule. The decision to unblind treatment allocation is at the discretion of the DSMC. The DSMC provides a recommendation in a report to the trial coordinators. The decision to terminate or continue the study will be made in consultation with the participating centres.

### Subgroup analyses

Pre conceived subgroup analyses are planned for age (under and over 30 years), history of a previous EP, pre-operative serum hCG-level (< 3,000 IU/l, 3,000–6,000 IU/l, and > 6,000 IU/l), and size of the ectopic mass (less or more than 4 cm).

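### Age, pre-operative hCG and mass size are planned as banded subgroups; if effect modification is judged from the bands, information on a smooth change in treatment effect is lost

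*Protocol article*

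**What the plan says.** The Subgroup analyses section of the protocol article is one sentence. It states that "Pre conceived subgroup analyses are planned" for four factors:

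- age, as "age (under and over 30 years";
- history of a previous ectopic pregnancy (EP), which is binary by nature;
- hCG, as "pre-operative serum hCG-level (< 3,000 IU/l, 3,000–6,000 IU/l, and > 6,000 IU/l";
- mass size, as "size of the ectopic mass (less or more than 4 cm".

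The sentence gives no reason for the cut-points, no distribution of the measurements, no test and no outcome. The Statistical analysis section says that the treatment effect on future fertility is a fecundity rate ratio (FRR) "calculated through Cox proportional hazard analysis", and that short-term outcomes are given as relative risks. The Sample size section states that "225 patients in each group are required", sized for the overall comparison.

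**The concern.** Banding treats all women within a band as alike and puts a step at each cut-point. A woman at 2,900 IU/l is separated from one at 3,100 IU/l and grouped with one at 100 IU/l. If the relative merit of the two operations changes gradually with hCG, mass size or age, the bands discard part of the evidence for that change, and each band estimate rests on a fraction of the events. The trial is sized for the main comparison, so power for effect modification is limited from the outset. The article's Discussion says that the results should guide clinicians' choice of operation, so a real gradient would be worth finding.

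There is also a wording gap. Read literally, the age and mass-size groups have no place for a woman of exactly 30 years or a mass of exactly 4 cm. The hCG bands do not have this gap: both 3,000 and 6,000 IU/l fall in the middle band.

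**Working it through.** The article gives no figure for subgroup information or power, so there is none to reproduce.

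**Inputs.** The cut-points come from the Subgroup analyses section. The two-sided 5% level and 80% power are the conventions of the Sample size section ("significance level of 5%, a power of 80"%), used here only as a yardstick. The covariate distributions are my assumptions: normal for age and mass size, and log-normal for hCG with median 2,000–3,000 IU/l and geometric SD 3–3.5. The interaction is assumed linear in the covariate (in log hCG for hCG).

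**Information kept.** For a linear interaction, the fraction kept is the between-band variance divided by the total variance. For a standard normal covariate with band limits a < b:

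kept = Σ [φ(a) − φ(b)]² / [Φ(b) − Φ(a)]

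**hCG, three bands, one case in full.** Take median 2,000 and geometric SD 3.

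- Standardised cuts: ln(3,000/2,000)/ln 3 = 0.369 and ln(6,000/2,000)/ln 3 = 1.000.
- Band shares: 64%, 20%, 16%.
- Contributions: 0.216 + 0.087 + 0.369 = 0.67 kept, a loss of 33%.

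All four corners of the assumed range:

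| Median (IU/l) | Geometric SD | Shares (%) | Kept | Loss |
|---|---|---|---|---|
| 2,000 | 3 | 64 / 20 / 16 | 0.67 | 33% |
| 2,000 | 3.5 | 63 / 18 / 19 | 0.68 | 32% |
| 3,000 | 3 | 50 / 24 / 26 | 0.745 | 25.5% |
| 3,000 | 3.5 | 50 / 21 / 29 | 0.74 | 26% |

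Other shares move the result. Tertiles lose 21%, and the best possible three-band split (27/46/27) loses 19%.

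**Age and mass size, two bands.** With a share q below the cut c, kept = φ(c)² / [q(1 − q)].

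- 50/50: 0.1592/0.25 = 0.637, a loss of 36%, the smallest possible for a normal covariate.
- 40/60: loss 38%.
- 30/70: loss 42%.
- 20/80: loss 51%.

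**Dependence on the normal assumption.** A uniform covariate loses 25% at a median split and 11% at tertiles.

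**Power for an hCG interaction.** An interaction with 80% power on 1 df as a continuous term has noncentrality (1.960 + 0.842)² = 7.85. Banding multiplies this by the fraction kept: 7.85 × 0.671 = 5.27 and 7.85 × 0.745 = 5.85.

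- 1-df trend across bands, scored at the band means: 63–68% power.
- 2-df test of the three bands: 53–57% power.

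**Size of the boundary gap for age.** With age in completed years, an assumed mean of 27–33 and SD of 4–6, about 5–10% of women are 30. That is about 25–45 of 2 × 225 = 450. No such figure can be given for 4 cm, because the article says nothing about how mass size is distributed or recorded.

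**The case against.** The strongest objection is that this is a condensed article whose analysis plan is not shown. The subgroup sentence does not say that the measurements will be used only as bands, and a continuous interaction term may be specified elsewhere. That stands: nothing here can be called an omission, and the loss arises only if effect modification is judged from the bands. It is also true that cut-points fixed in advance are conventional and guard against data-driven cuts, and that if the true effect is a step near a cut-point, a linear term could do worse than the bands.

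Stronger readings are tempting, and the document does not support them:

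- A reader might infer a single loss, such as a quarter to a third, for all three measurements. That range fits hCG under the distribution assumed above. A two-band split of a normal covariate loses more, tertiles lose less, and the article gives no distribution at all.
- A reader might take 53–57% as the power under the plan. No 2-df test is specified; with a 1-df trend about 10 points of that drop disappear.
- A reader might suppose that sizes are rounded to whole centimetres and that 4 cm is therefore common. The article says nothing on this.
- A reader might treat the gaps at 30 years and 4 cm as a substantive flaw. They are real, but an analyst would fill them sensibly; on their own they are a detail of wording.

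**Conclusion.** The point holds as a cheap improvement. Three continuous measurements are fixed as bands for planned subgroup analyses, and if effect modification is judged from those bands, roughly 20–40% of the information on a linear interaction is lost when the bands are reasonably balanced. Unbalanced two-band splits lose more, and a uniform covariate can lose less. These figures rest on assumed distributions and on linearity; only the banding and the two boundary gaps are read directly from the text. The loss concerns the subgroup comparisons alone. The primary analysis and the sample size are untouched.

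**What to change.** - Test effect modification with a treatment-by-continuous-covariate term for log hCG, mass diameter and age, in the model used for the outcome concerned: Cox for time to spontaneous intrauterine pregnancy and for repeat EP, and a relative-risk model for short-term outcomes such as persistent trophoblast.
- Report the treatment effect with its 95% CI across the range of each covariate.
- Keep the bands for display and as a check on the assumed form.
- Make the display bands exhaustive, for example < 30 v ≥ 30 years and < 4 v ≥ 4 cm.

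The cost is a few lines of analysis text. It needs no new model class for the fertility outcomes and no extra data, provided that the measured values themselves are recorded and not only the band. The downside is dependence on the chosen functional form, which the banded display helps to check.
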